#### ***4.10. Procedure for keeping and unblinding randomization codes***

As the study is double-blind, the study product and the reference product will be identified only by lot number on the packs. JSC BIOCAD will prepare randomization envelopes with the information unblinding the therapy arm codes for each drug lot. The envelopes will be provided to the study site and stored in the Investigator's File or in a limited access place. The investigator is allowed to unblind the treatment only in case of an emergency. The investigator must exercise his/her best efforts to prevent the loss or unblinding of study codes when unnecessary.

The treatment can be unblinded only in case of an emergency, when this is necessary to give an appropriate treatment to the patient and ensure his/her well-being. If a medical situation that requires unblinding occurs, the principal investigator must contact a representative from JSC BIOCAD (medical expert, pharmacovigilance officer, or clinical study manager) specify the reasons for unblinding reasons and obtain an approval for this procedure. All the contact information is presented on the title page of this Protocol. If JSC BIOCAD approves unblinding, the investigator unblinds a study code, records this fact in the source document, and notifies the clinical study manager by phone or e-mail

All patients participating in the study will receive Subject ID cards containing the protocol code, study site number, investigator's contact information, contact information of the BIOCAD's responsible medical officer and pharmacovigilance officer (available 24 h daily). Patients should be aware that they should carry their Subject ID cards all the time and notify medical staff at any other medical facility that they participate in this clinical study. If necessary (for example, to administer another medicinal product), a physician at another medical facility (other than the study center) can contact the investigator to discuss benefits and potential risks related to concomitant therapy.

#### ***4.11. Data entered directly into CRF (i.e. no prior written or electronic record of data) and considered as source data***

All data entered to the CRF must be recorded in the source documentation.

In this study, no data will be entered directly to the CRFs without prior entering to the source documents.

## 5. Eligibility and exclusion of study subjects

### 5.1. Inclusion criteria

1. The patient signed the informed consent form.
2. The patient is 18 to 75 years old at screening.
3. The patient has moderate-to-severe plaque psoriasis and was diagnosed at least 6 months before signing the informed consent form.
4. The patient received at least one course of phototherapy or systemic therapy for psoriasis and, in the opinion of the investigator, responded inadequately, or the patient was a candidate for any of these therapies.
5. The BSA  $\geq 10\%$ , PASI  $\geq 12$ , and sPGA  $\geq 3$  at screening.
6. Laboratory values at screening:
  - Hb  $\geq 10$  g/dL (100 g/L)
  - WBC count  $\geq 3000/\mu\text{L}$  ( $3.0 \times 10^9/\text{L}$ )
  - Platelet count  $\geq 100\,000/\mu\text{L}$  ( $100 \times 10^9/\text{L}$ )
  - Neutrophil count  $\geq 2000/\mu\text{L}$  ( $2 \times 10^9/\text{L}$ )
  - AST, ALT, and alkaline phosphatase  $\leq 2.5 \times \text{ULN}$
  - Serum creatinine  $< 176.8 \mu\text{mol/L}$  (2.0 mg/dL)
7. The patient tested negative for serum and virologic markers of active and latent hepatitis B (HBV) and hepatitis C (HCV).
8. The patient has a negative urine pregnancy test at screening (the test is not performed for women who are post-menopausal for at least 2 years or those who underwent surgical sterilization).
9. The patient tested negative for tuberculosis:
  - The negative result of the QuantiFERON or T-Spot.TB.OR
  - The negative result of the Diaskintest®.
10. Patients with indeterminant and/or positive results of the QuantiFERON/Diaskintest® are allowed in the study only if all of the following three criteria are met:

---

 The screening examination includes tests for HBsAg and total antibodies to HBcor antigen (IgG+IgM). If the patient tested negative for these markers (HBsAg and anti-HBcor total), he/she is considered eligible for the study with respect to this criterion. If the patient tested positive for HBsAg, the patient cannot be included in the study regardless of the results for anti-HBcor. If the patient tested negative for HBsAg but positive for anti-HBcore-total, the patient has to undergo additional examinations. Additional examinations include but were not limited to the following: qualitative PCR for HBV DNA, anti-HBcor-IgG, anti-HBcor-IgM, blood biochemistry, and a consultation with an infectious disease specialist. Having considered the examinations and test results, the Sponsor decides whether to approve such a patient for the study.

 The screening examination includes a test for anti-HCV antibodies in the blood. If the patient tests negative for anti-HCV, he/she is considered eligible for the study with respect to this criterion. If the patient tests positive for anti-HCV, the patient has to undergo additional examinations. Additional examinations include but were not limited to the following: qualitative PCR for HCV RNA, blood biochemistry, and consultation with an infectious disease specialist. Having considered the examinations and test results, the Sponsor decides whether to approve such a patient for the study.

- The patient tests negative in one additional QuantiFERON / T-Spot.TB assay.
  - No signs of active tuberculosis are seen on the chest X-ray (or fluorography or CT or MRI) done any time within 1 month before signing the informed consent form.
  - The TB specialist reported that the patient has no tuberculosis. The report has to be obtained during the screening.
11. The investigator considers the patient able to carry out all the procedures per protocol.
  12. The patient and his/her sexual partner with retained reproductive potential are ready to implement reliable contraception throughout the screening period (starting from signing the informed consent) and during four weeks after the last dose of BCD-057/Humira®. This requirement does not apply to the patients who had undergone surgical sterilization. Reliable contraception means one barrier method in combination with one of the following: spermicides, intrauterine device and/or oral contraceptives used by the patient or patient's partner.

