|          | 
7. The patient tested negative for serum and virologic markers of active and latent hepatitis B (HBV) and hepatitis C (HCV).
 
8. The female patient has a negative urine pregnancy test at screening (the test is not performed for women who are post-menopausal for at least 2 years or those who underwent surgical sterilization).
 
9. The patient tested negative for tuberculosis:
 
 
• The negative result of the QuantiFERON or
 
• T-Spot.TB.
 
 
OR
 
 
• The negative result of the Diaskintest®.
 
 
10. Patients with indeterminant and/or positive results of the QuantiFERON /T-Spot.TB / Diaskintest® are allowed in the study only if all of the following three criteria are met:
 
 
• The patient tested negative in one additional QuantiFERON or T-Spot.TB assay.
 
• No signs of active tuberculosis are seen on the chest X-ray (or fluorography or CT or MRI) done any time within 1 month before signing the informed consent form.
 
• The TB specialist reported that the patient has no tuberculosis. The report has to be obtained during the screening.
 
 
11. The investigator considers the patient able to carry out all the procedures per protocol.
 
12. The patient and his/her sexual partner with retained reproductive potential are ready to implement reliable contraception throughout the screening period (starting from signing the informed consent) and during four weeks after the last dose of BCD-057/Humira®. This requirement does not apply to the patients who had undergone surgical sterilization. Reliable contraception means one barrier method in combination with one of the following: spermicides, intrauterine device and/or oral contraceptives used by the patient or patient's partner.
 |

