#### ***4.5. Expected duration of the study and subjects’ participation in the study***

The expected duration of the study is 30 months. This includes patient recruitment (up to 12 months), treatment period, follow-up period, and collection and statistical processing of results.

Each subject will participate in the study for up to 59 weeks (about 14 months), including 4 weeks of screening, 51 weeks of treatment, and 4 weeks of follow-up.

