| Day                                                                                                                                                                                                                     |           | 1 | 1                | 1 | 1 | 1 | 1 | 1 | 1 | 1 | 2                | 3                | 4                | 5                | 6                | 7                | 1  | 2                 | 4                 | 6                 | 1  | 1  | 1  | 1  | 1  | 1  | 1  | 1  | 1  | 1  | 1  | 1  | 1           | 1  | 1  | 1  | 1  | 1  | 1  | 1  |
| 7 Pregnancy test is carried out with the urine HCG test strips. The pregnancy test is not required if the patient is at least 2 years post-menopausal or had a uterus or ovary surgery that makes pregnancy impossible. |           |   |                  |   |   |   |   |   |   |   |                  |                  |                  |                  |                  |                  |    |                   |                   |                   |    |    |    |    |    |    |    |    |    |    |    |    |             |    |    |    |    |    |    |    |
| 8 The patient fills out the questionnaires on the visit day before receiving an injection of BCD-057/Humira® (if applicable).                                                                                           |           |   |                  |   |   |   |   |   |   |   |                  |                  |                  |                  |                  |                  |    |                   |                   |                   |    |    |    |    |    |    |    |    |    |    |    |    |             |    |    |    |    |    |    |    |
| 9 Only SAEs are documented.                                                                                                                                                                                             |           |   |                  |   |   |   |   |   |   |   |                  |                  |                  |                  |                  |                  |    |                   |                   |                   |    |    |    |    |    |    |    |    |    |    |    |    |             |    |    |    |    |    |    |    |

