#### **4.6.2. Procedures by visits**

##### ***Procedures of the screening period***

The Screening Period starts from the moment the patient signs the informed consent form and continues for not more than 4 weeks (Days -28 to 0) until the day when the patient is included in the study. The Screening Period includes the following procedures:

- Signing the informed consent form.
- Demographic data, life and disease history.
- Data about concomitant therapy.
- Physical examination.
- Body weight.
- BP, wrist pulse, and body temperature.
- ECG.
- Chest x-ray / fluorography.
- Diaskintest® / QuantiFERON test / T-Spot.TB.
- CBC (at least 2 mL of blood).
- Blood biochemistry (at least 4 mL of blood).
- Urinalysis.
- Tests for HIV, HCV, HBV, syphilis (at least 12 mL).
- BSA.
- PASI score.
- Static Physicians Global Assessment (sPGA).
- NAPSI.
- Itch intensity VAS score (0 to 100 mm).
- Pregnancy test (HCG in urine, test strip).
- Checking for eligibility (inclusion/exclusion criteria).
- Inclusion in the study (randomization for Period I).
- Documenting, recording, and reporting SAEs.

Total blood volume taken at the visit: at least 18 mL.

---

 If the QuantiFERON assay is done during this visit, the volume of blood taken will be at least 4 mL.

 If the T-Spot.TB assay is done during this visit, the volume of blood taken will be at least 6 mL.

 At screening, the test can be repeated once if the first result did not meet the eligibility criteria.

 Pregnancy test is carried out only in women. The urine HCG is measured with a test strip. The pregnancy test is not required if the patient is at least 2 years post-menopausal or had a uterus or ovary surgery that makes pregnancy impossible.

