| Pregnancy test            | Urine HCG (only in women of childbearing potential; not applicable to post-menopausal women).                                                                                                                                                                                                                                                                                                                                                                                                                                                                                                                                                                                                                                                                                                           | $\times 1$ : at screening                                                                                                                                                                                        | Study site                                                 |
| Instrumental examinations | ECG                                                                                                                                                                                                                                                                                                                                                                                                                                                                                                                                                                                                                                                                                                                                                                                                     | $\times 3$ :
at screening,                                                                                                                                                                                    | Study site or an external clinic                           |

 HIV, HBV, HCV, and syphilis test results are considered valid for screening if they were obtained within 1 month before signing the ICF and if the test result fully meets the requirements of this Protocol.

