#### 4.7.1. History taking, complaints, demographics

The following parameters will be documented based on the patient's medical records and questioning:

- Date of birth
- Gender
- Age
- Ethnic origin
- Reproductive potential (use of contraception with methods specified, menopause and its duration, sterilization, if applicable)

- Prior and/or concurrent diseases (infections, chronic infections and inflammatory diseases, tuberculosis, contacts with a tuberculosis patient, immune deficiency, concurrent conditions, allergic reactions) with dates of onset/resolution (if applicable).
- Psoriasis history (approximate date of onset, approximate date of diagnosis, number and duration of relapses and remissions, triggering factors, insolation).
- Medication history:

A) Specify all medications that the patient has received for the treatment of psoriasis, with doses, dosing regimens, therapy duration, and effectiveness of each medication as judged by the investigator. If the medication was discontinued, specify the reason. To assess whether the patient is eligible for the study, a history of the following medications should be elucidated:

- Systemic oral anti-infectious agents within 28 days before signing the informed consent form.
- Systemic IV and/or IM anti-infectious agents within 8 weeks before signing the informed consent form.
- Adalimumab or any other inhibitors of tumor necrosis factor alpha.
- Two or more biologics for the treatment of psoriasis.
- Systemic glucocorticoids, systemic retinoids (acitretin) within 4 weeks before signing the informed consent form.
- Systemic non-biologic medications including (but not limited to) methotrexate, sulphasalazine, cyclosporine, apremilast, mycophenolate mofetil, etc. within 4 weeks before signing the informed consent form; OR leflunomide or cyclosporine within 6 months before signing the informed consent form.
- Phototherapy [including selective phototherapy (UVB) and photochemotherapy (PUVA)] within 4 weeks before signing the informed consent form,
- Vaccination with live or attenuated vaccines within 8 weeks before signing the informed consent form.

B) Specify any medications that the patient has received within 30 days before screening. Specify the dose, dosage regimen, treatment duration, and reason for discontinuation (if applicable).

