#### ***4.8.2. Criteria for premature withdrawal of study subjects***

The patient will be withdrawn from the study in the following circumstances:

1. A major violation of inclusion/exclusion criteria is revealed after the patient was enrolled in the study (withdrawn by the decision of JSC BIOCAD).
2. The patient recalls his/her consent to participate in the study.
3. The patient develops adverse events or serious adverse events, laboratory abnormalities or comorbidities that, in the investigator's opinion, make further participation in the study

---

 Deviations from inclusion/exclusion criteria justified by the investigator and approved by the Sponsor are not considered a reason for withdrawal.

impossible, dangerous or non-beneficial regarding patient's well-being and/or safety.

4. The patient misses more than 4 injections and/or visits during the study (compliance < 85%) or misses 2 consecutive injections and/or visits, or breaches the specified time windows for more than 5 visits.
5. The patient develops active tuberculosis. If the patient has indeterminant or positive results of the QuantiFERON assay or T-Spot.TB or Diaskintest® at Week 25, he/she can continue the study only if all three of the following requirements are met:
  - The patient tests negative in one additional QuantiFERON / T-Spot.TB assay.
  - The chest X-ray shows no signs of active tuberculosis.
  - The TB specialist confirms that the patient has no tuberculosis.Otherwise, the patient has to be removed from the study.
6. The patient gets pregnant. If pregnancy is suspected, the urine test for HCG must be performed. If the test gives a positive result, the patient must be withdrawn from the study (follow-up procedures are described in section 5.4).
7. The patient has a major depressive disorder or suicidal ideation or makes suicidal attempts.
8. The study is terminated by JSC BIOCAD, local ethics committees, or regulatory authorities.
9. The patient uses medications prohibited by the Protocol.
10. The patient dies.

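### Inclusion criterion 12 asks for contraception during screening and after the last dose but not during the 51 weeks of treatment, and Table 19 drops the 2-year menopause limit on the pregnancy test

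*Protocol*

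**What the plan says.** **Contraception.** Inclusion criterion 12 in Protocol section 5.1 requires that the patient and partner be "ready to implement reliable contraception throughout the screening period (starting from signing the informed consent) and during four weeks after the last dose". The synopsis gives the same interval: "throughout the screening period (starting from signing the informed consent) and during four weeks after the last dose". Surgically sterilized patients are exempt.

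**Study periods.** Under section 4.6.2 the screening period "continues for not more than 4 weeks (Days -28 to 0) until the day when the patient is included in the study". Section 4.5 gives each subject's participation as up to 59 weeks, "including 4 weeks of screening, 51 weeks of treatment, and 4 weeks of follow-up".

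**Other text on contraception and pregnancy.**
- Section 4.7.1 lists contraception among the history items: "Reproductive potential (use of contraception with methods specified, menopause and its duration, sterilization, if applicable".
- Exclusion criterion 17 (section 5.2) bars women who are pregnant, breastfeeding or planning a pregnancy during the study.
- Section 4.8.2, item 6, covers pregnancy on study: "If pregnancy is suspected, the urine test for HCG must be performed". A positive result means withdrawal.
- Table 18 schedules the pregnancy test at screening only.

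**Who is exempt from the pregnancy test.** Table 19 says the test is done "only in women of childbearing potential; not applicable to post-menopausal women". Note 7 to Table 18 says instead: "The pregnancy test is not required if the patient is at least 2 years post-menopausal", or has had surgery that rules pregnancy out. Inclusion criterion 8 sets the same 2-year limit.

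**The concern.** Criterion 12 joins two intervals with the word *and*; it does not describe a span with a start and an end. The part left out is the time on adalimumab, which is the exposure the criterion presumably exists to guard against. A site that applies and documents the criterion as worded obtains no commitment to contraception for the weeks on drug.

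The protocol itself treats pregnancy on treatment as serious. Section 8.1.1.2 requires therapy to stop at once and the exposure to be followed up as an SAE is. Sections 5.4.1 and 8.4 follow mother and child to 6 months after delivery, and section 8.4 also covers pregnancies in partners. An eligibility rule that leaves out the dosing period sits badly with this.

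The Table 19 entry is a separate and smaller fault, but it is a direct contradiction on an eligibility test. Criterion 8 requires a negative test from a woman less than 2 years post-menopausal, and Table 19 says the test does not apply to her. Section 4.7 presents that table as the list of scheduled procedures, so a site could well work from it.

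**Working it through.** **1. Participation time.** Section 4.5 gives 4 weeks of screening, 51 of treatment and 4 of follow-up: 4 + 51 + 4 = 59 weeks, which agrees with the stated 59.

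**2. What criterion 12 names.** Screening ends at inclusion (section 4.6.2), so the first interval is at most 4 weeks. The second is the 4 weeks after the last dose, which coincide with the follow-up period (Week 51 to Week 55).
- Named: 4 + 4 = 8 weeks; 8/59 = 13.6%.
- Not named: 59 − 8 = 51 weeks; 51/59 = 86.4%.

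**3. Dosing inside the unnamed interval** (regimen in section 4.4.1).
- Week 0, then odd weeks 1 to 23: 1 + 12 = 13 dosing visits.
- Odd weeks 25 to 51: (51 − 25)/2 + 1 = 14 dosing visits.
- Total: 13 + 14 = 27, which is every dosing visit in the study.

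**4. Does other text close the gap?**

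| Place | What it does | Requires contraception on treatment? |
|---|---|---|
| Section 4.7.1 | Records contraceptive methods in the history | No |
| Exclusion 17 (section 5.2) | Bars existing or planned pregnancy | No |
| Table 18 | One pregnancy test, at screening | No |
| Sections 4.8.2 and 5.3, item 6 | Test on suspicion; withdrawal if positive | No |
| Section 8.1.1.2 | Stops therapy once pregnancy is confirmed | No |
| Sections 5.4.1 and 8.4 | Follow-up of pregnancy and child | No |

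**5. Pregnancy-test exemption, place by place.**

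| Place | Menopause limit |
|---|---|
| Synopsis, criterion 8 | At least 2 years |
| Synopsis, study procedures | At least 2 years |
| Section 4.2, study procedures | At least 2 years |
| Table 18, note 7 | At least 2 years |
| Section 4.6.2, screening footnote | At least 2 years |
| Section 5.1, criterion 8 | At least 2 years |
| Table 19 | None stated |

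Six places agree and Table 19 alone differs. Its restriction to women of childbearing potential does not restore the limit, because the same cell goes on to exempt post-menopausal women without qualification.

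**The case against.** The strongest reply is that nobody would read criterion 12 that way. It names a start (consent) and an end (four weeks after the last dose), and a site is unlikely to conclude that two contraceptive methods are needed before the first dose and after the last but not in between. On that view the 86% measures a reading nobody intended. Exclusion 17 runs through the whole of participation, pregnancy leads to withdrawal, and the patient information sheet and consent form, which are not available here, may state the requirement in full. On Table 19, criterion 8 governs, and the sponsor reviews the Screening Form before randomization (section 4.7.18), so a missed test could be caught.

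Much of this is fair. The intent is very probably continuous contraception, and no evidence shows that any site would do otherwise. What patients are actually told cannot be judged without the consent form. The Table 19 entry is an editorial mismatch with a second check behind it: a site could skip the test, not necessarily would. The absence of scheduled tests after screening is the sponsor's choice; it shows only that the schedule does not make up for the missing words.

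The defect in the wording remains. Exclusion 17 deals with planned pregnancy and asks for no contraception, so it does not address an unplanned one. The withdrawal, discontinuation and follow-up rules act only after pregnancy is suspected or confirmed. If the consent form does state the full interval, the protocol should match it.

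**Conclusion.** Criterion 12 is wrong as written, in both the synopsis and section 5.1. Taken literally it covers 8 of 59 weeks and omits the 51 weeks containing all 27 dosing visits, and nothing else visible in the protocol supplies the missing requirement. Table 19 contradicts six other statements of the pregnancy-test exemption.

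Confidence is high on the wording. The practical consequence depends on how sites read the criterion and on a consent form that cannot be seen here. This is a matter of subject safety and internal consistency; it does not touch the sample size, power, type I error or the primary analysis. It should be corrected at the next amendment.

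**What to change.** 1. In the synopsis and in section 5.1, change the interval in criterion 12 to: *from signing the informed consent, throughout the treatment period, and until four weeks after the last dose of BCD-057/Humira®*. This covers all 59 weeks.
2. In Table 19, replace the blanket post-menopausal exemption with the one in criterion 8 and Table 18 note 7: at least 2 years post-menopausal, or surgery that makes pregnancy impossible.
3. Check that the patient information sheet and consent form give the same contraception interval.

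The four-week end point can stay; its length is the sponsor's judgement. The cost is one sentence in two places, one table cell and one document check, with no new visit, test or procedure.
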